### Sample size

The sample size was calculated on the basis of the primary hypothesis. In the exploratory study [22], those referred to PEPS had a greater improvement in social functioning at 6 month follow-up equivalent to 1.05 points on the SFQ. However, a number of people received PEPS who were not included in the trial (e.g., the wait-list control) and, for this larger sample (N = 93), the mean pre-post- treatment difference was 1.79 (pre-treatment mean = 13.85, SD = 4.21; post-treatment mean = 12.06, SD = 4.21). (Note: a lower SFQ score is more desirable). This difference of almost 2 points accords with other evidence that this is a clinically significant and important difference [29]. A reduction of 2 points or more on the SFQ at 1 year follow-up in an RCT of cognitive behaviour therapy in health anxiety was associated with a halving of secondary care appointments (1.24.vs 0.65), a clinically significant reduction in the Hospital Anxiety and Depression Scale (HADS [30]) Anxiety score of 2.5 (9.9 vs 7.45) and a reduction in health anxiety (the main outcome) of 5.6 points (17.8 vs 12.2) (11 is a normal population score and 18 is pathological) [29]. These findings suggest that improvements in social functioning may accrue over 1 year, hence we expect to find a greater magnitude of response at the 72 week follow-up than we did in the exploratory trial. Therefore, we have powered this trial to be able to detect a difference in SFQ score of 2 points. SFQ standard deviations vary between treatment, control, and the wait-list samples, ranging from 3.78 to 4.53. We have based our sample size estimate on the most conservative (i.e., largest) SD. To detect a mean difference in SFQ score of 2 point (SD = 4.53) at 72 weeks with a two-sided significance level of 1% and power of 80% with equal allocation to two arms would require 120 patients in each arm of the trial. To allow for 30% drop out, 170 will be recruited per arm, i.e., 340 in total. We have considered the need to take clustering effects by therapy group into account. In this study, as in the pilot, participants are individually randomised to the treatment arms, and the observed SD of the response in the intervention arm automatically includes the effect of the clustering by therapist. The analysis will take account of this by using a hierarchical model to allow explicit estimation of the between therapy group variance.

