### Analyses

Demographic and other baseline data will be summarised by descriptive statistics (number [N], mean, standard deviation [SD], median, minimum and maximum) or frequency tables, stratified by treatment. Measures of adherence to protocol implementation will be summarised by descriptive statistics (number [N], mean, standard deviation [SD], median, minimum and maximum) or frequency tables, stratified by treatment arm. Efficacy will be assessed on the full analysis set, defined as all randomised participants for whom a post-baseline assessment of the primary endpoint is available, that is, in accordance with the "intention to treat" (ITT) principle. The primary efficacy parameter will be the difference in mean SFQ score between treatment arms, estimated using a hierarchical regression model with adjustment for relevant covariates, including centre, sex and personality disorder classification. Differences in mean totals of secondary outcomes at 72 weeks from randomisation will be compared between the two treatment arms, after adjusting for design (centre and sex) covariates. Analyses will be performed using Stata version 11 or above.

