The costs of the interventions will be estimated by combining data on number of sessions provided with unit costs derived from local data on service expenditure and activity. These costs will include therapist time, oncosts, overheads and capital. Costs of other services will be calculated by combining service use data collected with the CSRI with appropriate unit costs. Costs will be compared between the two groups, with bootstrap methods used to generate confidence interval round the difference due to the expected skewed cost distribution. Cost-effectiveness will be assessed by combining the cost adapt with outcomes, namely SFQ scores and Quality-Adjusted Life Years (QALYs). If the costs for the PEPS arm are less than for TAU and the outcome better, then it will be the 'dominant' intervention. However, if costs are greater and outcomes better, then an incremental cost-effectiveness ratio will indicate the extra costs incurred to achieve an extra unit-improvement in outcome (i.e., a one-point improvement on the SFQ or one extra QALY). There will be uncertainty around the point estimates of cost and outcome differences and this uncertainty will be explored by generating a large number of cost-outcome combinations using bootstrapped resample and plotting these on a cost-effectiveness plane. Cost-effectiveness will be interpreted using cost-effectiveness acceptability curves. These will show the probability that PEPS is more cost-effective intervention than TAU for a range of values placed on a unit-improvement in outcome. The range of values for a one-point improvement on the SFQ is unclear, but will be chosen such that we will be able to observe the points at which there is at least at 50% and 80% probability of PEPS being cost-effective. The range of values for a gain of one QALY is more straightforward as it appears that the value that informs NICE recommendations is between £20-30K. Therefore we will use a range of £0-£100K to produce the curve so as to include this threshold.

Thematic analysis methods will be used to specify the nature of treatment-as-usual in terms of what problem was treated by which service/professional and how. Thematic analysis methods will be used to identify themes in participants' opinions of PEPS therapy and TAU.

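### The sample size allows nothing for therapy-group clustering because it treats the observed SD as already covering it, so the stated 80% power at the 1% level holds only if the intraclass correlation is essentially zero

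*Protocol article*

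**What the plan says.** All of the sample size inputs are in the protocol article, Method, Sample size. For a target difference of 2 SFQ points at 72 weeks, an SD of 4.53 and a two-sided 1% level, the section states that "power of 80% with equal allocation to two arms would require 120 patients in each arm of the trial". Attrition is then added, in these terms: "To allow for 30% drop out, 170 will be recruited per arm, i.e., 340 in total". The SD of 4.53 is the largest in a range of 3.78 to 4.53 seen across treatment, control and wait-list samples.

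The section then turns to clustering by therapy group. It notes that participants are individually randomised and says that "the observed SD of the response in the intervention arm automatically includes the effect of the clustering by therapist". It gives no design effect, group size or ICC. The next sentence commits the analysis to a hierarchical model that estimates the variance between therapy groups, and the Analyses section makes hierarchical regression the primary method. The Interventions section describes the problem-solving component as 12 group sessions, given in the PEPS arm only.

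**The concern.** The sentence on the SD confuses two quantities. The SD of individual scores is a total: between-group plus within-group variance. Power depends on the variance of the arm mean. When PEPS participants share groups, their scores move together and the mean is less precise than SD/√n, even if the SD is measured perfectly. Individual randomisation does not prevent this, because the grouping arises after allocation.

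The two halves of the plan therefore do not match. The sample size uses a standard error without the group effect, and the planned model uses one with it. The passage also moves between therapist and therapy group as the cluster, and these need not be the same unit. What is at stake is how a null or borderline result is read: it would be judged against 80% power that the planned analysis may not have.

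**Working it through.** **Inputs from the Sample size section:** difference 2; SD 4.53; two-sided 1% (z = 2.576); 80% power (z = 0.842); 170 recruited per arm; 30% drop-out.

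**Assumptions, because the article gives neither:** m = 6 or 8 analysed per therapy group; ICC = 0.02, 0.05 or 0.10. TAU participants are treated as unclustered.

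**1. Reproduce the plan's figure.** Under independence, n = 2(2.576 + 0.842)² × 4.53² / 2² = 119.8 with unrounded normal quantiles, so 120 per arm (power 80.07%). The recruited number leaves 170 × 0.7 = 119 evaluable: SE = 4.53 × √(2/119) = 0.587, 2/0.587 = 3.406, and Φ(3.406 − 2.576) = 79.7%. (Strictly, 120/0.7 = 171.4, so 172; the difference is immaterial.) At the stated inputs nothing is held in reserve for clustering.

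**2. Variance with groups in one arm.** Write total variance SD² = σ²(between) + σ²(within), with ICC = σ²(between)/SD². For n patients in groups of m,

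Var(PEPS mean) = SD² × [1 + (m − 1)ICC] / n,

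so SE(difference) = SD × √[(1 + DE)/n], with DE = 1 + (m − 1)ICC. The SD is 4.53 throughout; only the correlation changes.

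**3. Power with 119 per arm.** For m = 6 and ICC = 0.05: DE = 1 + 5 × 0.05 = 1.25; SE = 4.53 × √(2.25/119) = 0.623; 2/0.623 = 3.211; Φ(3.211 − 2.576) = 73.7%. All settings:

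| m | ICC | DE | SE | Power (normal) | Power (small-sample df) |
|---|---|---|---|---|---|
| 6 | 0.02 | 1.10 | 0.602 | 77% | 74% |
| 6 | 0.05 | 1.25 | 0.623 | 74% | 70% |
| 6 | 0.10 | 1.50 | 0.657 | 68% | 64% |
| 8 | 0.02 | 1.14 | 0.607 | 76% | 72% |
| 8 | 0.05 | 1.35 | 0.637 | 71% | 67% |
| 8 | 0.10 | 1.70 | 0.682 | 64% | 58% |

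The last column uses a noncentral t with Satterthwaite degrees of freedom. The true SE is 2% to 16% larger than the independence value of 0.587.

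**4. Simulation check.** 20,000 trials per setting were run with 120 per arm, m = 8, total SD held at about 4.5, and a group-mean Satterthwaite test. Power was 76.5% at ICC 0, 66.5% at 0.05 and 58.8% at 0.10. The starting value is below 80% because that test has few groups to work with. The fall from there occurs although the SD of individual scores hardly changes, which is direct evidence against the protocol's sentence.

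**5. Margin in the SD.** The article reports SD 4.21 in its larger sample of 93 people who received PEPS. With 119 per arm and ICC 0.05: m = 6 gives SE = 4.21 × √(2.25/119) = 0.579 and power 81%; m = 8 gives SE = 4.21 × √(2.35/119) = 0.592 and power 79%. With m = 8 and ICC 0.10 it is 72%.

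**The case against.** Four points on the other side carry weight.

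- **The size of the loss is not in the document.** Every clustered figure rests on an assumed group size and ICC. At m = 4 and ICC 0.01, power with 120 per arm is 79.4%, a loss of under one point. The Discussion also expects some drop-out before group therapy starts, and anyone followed up who never joined a group adds no group correlation. This stands: the shortfall can be given only as a conditional range.
- **The plan is conservative elsewhere.** Step 5 shows that the largest SD may absorb part or all of the loss. At a 5% level, power with 120 per arm would stay above 80% for m = 6 to 10 and ICC 0.05 to 0.10 (lowest 81.1%). This also stands, but the article presents the SD as cover for variation between samples, and its stated level is 1%. Any offset would be by luck.
- **The primary inference is protected.** The hierarchical model accounts for the group. A reader might infer that the primary test has an inflated type I error; the documents do not support that.
- **The secondary and cost analyses.** A reader might also infer that these ignore clustering, since secondary outcomes are compared "after adjusting for design (centre and sex) covariates" and the cost text says only "Costs will be compared between the two groups, with bootstrap methods used to generate confidence interval". That is an argument from silence. A list of covariates does not exclude a group effect, the bootstrap's resampling unit is not stated, and a condensed article commonly leaves both to the full protocol or SAP. It is no part of this point.

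The defence that articles condense does not reach the main point. The fault is a reason that the article states, and more detail elsewhere would not make that reason correct.

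**Conclusion.** The stated rationale is wrong, and 120 per arm is the independence figure. At SD 4.53 and the two-sided 1% level, the planned analysis reaches the stated 80% only if the ICC is essentially zero. For 6 to 8 analysed per group and ICC 0.02 to 0.10, power is about 64% to 77% by the normal formula and 58% to 74% with small-sample degrees of freedom. These figures rest on assumed group sizes and ICCs, all PEPS patients being grouped, and no gain from covariates.

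It would go too far to say flatly that the trial lacks 80% power: a true SD nearer 4.21, a very small ICC or a strong baseline covariate could each restore it. It would equally go too far to say that no extra patients are needed. That depends on the correlation between baseline and 72-week SFQ, which the article does not give, and baseline SFQ is not among the covariates it names.

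**What to change.** In the Sample size section:

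1. Replace the sentence on the SD with a correct statement: the SD includes between-group variance, but the precision of the PEPS mean also depends on group size and ICC.
2. Name therapy group as the cluster, in the PEPS arm only, with TAU participants unclustered.
3. State the expected number analysed per group and an assumed ICC range, with the source.
4. Restate the power of the 340-patient design from SE = SD × √[(1 + DE)/n] as a range, for example about 70% to 74% at ICC 0.05 with 6 per group and SD 4.53. If the largest SD is meant as a margin for clustering, say so and show the figures at 4.21.

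Adding baseline SFQ as a covariate may recover some or all of the loss. If it reduces both variance components in proportion, the SE is multiplied by √(1 − r²). Returning to the independence value then needs 1 − r² = 2/(1 + DE), so at ICC 0.05 r is about 0.33 for 6 per group (2/2.25) and 0.39 for 8 (2/2.35). With an assumed r = 0.5, power would be about 87% at m = 6, ICC 0.05, but about 79% at m = 8, ICC 0.10. The gain is smaller if baseline explains little of the between-group variance.

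For scale, keeping 80% at SD 4.53 by numbers alone, at ICC 0.05, would take 135 evaluable per arm with 6 per group (386 recruited in total) or 141 with 8 (404 in total).

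The cost is wording, a short calculation and a less favourable stated power.

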### Recruitment

To recruit the required number (N = 340), we estimated that we need to approach twice as many people (N = 680). This estimate is based upon the exploratory trial, in which 464 potential participants were approached to be invited to participate; of these, 316 (68%) volunteered to participate; 255 (55%) turned up for the assessment interview; 241 (52%) met the criteria and hence were available to be randomised. A recruitment flow chart is presented in Figure 1.

**Figure 1 F1:**
[figure not shown]
**Recruitment Flow Diagram**.

Three sites are participating in the trial. Each of the three sites needs to refer approximately 230 people to the project over 26 months (approximately 106 per year). Based on information about the sites, this was considered to be feasible. In West London, the two local Mental Health Trusts from which we are recruiting serve a population of 1.7 million people, with potentially 74,800 people with personality disorder. In 2007, one of the five boroughs received 80 referrals of people with personality disorder who were motivated to receive psychological treatment for their disorder. New specialist services were planned for 2009 in two of the other boroughs and similar rates of referral to these new services were expected. Cwm Taf NHS Trust serves a population of 330,000 with potentially 14,520 people with personality disorder. In 2007, there were 4,173 referrals per annum across two Community Mental Health Teams (CMHTs) and two crisis teams. A retrospective audit of randomly selected current case notes (N = 109) found that between 8 and13% of people seen by one CMHT met the DSM-IV criteria for borderline personality disorder. Therefore, an estimated 333 to 542 of the people annually referred to mental health services were expected to meet the diagnostic criteria for borderline personality disorder. Assuming that this figure represents between 30% and 60% of the population with personality disorders, it can be estimated that an additional number of between 133 and 217 people meet the criteria of a personality disorder other than borderline. Tees, Esk and Wear Valley NHS Foundation Trust serves a total population of 1.4 million across County Durham, the Tees Valley and North East Yorkshire. One existing advanced practitioner service for personality disorder covering a population of 100,000 received approximately 50 referrals per year, primarily from CMHTs, of individuals likely to benefit from psychological intervention. This service was planning to expand its remit to the larger area of North Durham (300,000 population) and Teesside (500,000 population), hence it was expected that an expanded service would receive up to 400 referrals annually for all personality disorders by the study start date, requiring a referral rate of the study of less than 25% to meet the target.

### Randomisation and blinding

Randomisation is based on a computer generated pseudo-random code using random permuted blocks of randomly varying size, created by the Nottingham Clinical Trials Unit (CTU) in accordance with their standard operating procedure and held on a secure server. The randomisation is stratified by recruiting centre and sex of participant. Access to the sequence is confined to the Trial Data Manager. Researchers access the treatment allocation for each participant by means of a remote, internet-based randomisation system developed and maintained by the Nottingham CTU. The sequence of treatment allocations will be concealed until interventions have all been assigned and recruitment, data collection, and all other trial-related assessments are completed. The trial is single-blind, with participants and local investigators administering the interventions being aware of the treatment allocation. Outcome measures are administered in a blinded fashion by researchers to minimise the effects of lack of blinding.

### Interventions

Psycho-education combined with problem solving (PEPS) therapy is a complex cognitive-behavioural intervention that integrates individual and group therapies. Psycho-education is an individual 4-session collaborative dialogue designed to build a rapport with patients, inform them about their personality disorder, discuss its effects on interpersonal relationships and social functioning, and enhance motivation for therapy [21]. In psycho-education, participants are taken through their personality disorder diagnoses, as identified via a structured clinical assessment. Participants are asked what problems they experience in relation to their personality disorder and they are then guided to specify problems which are then prioritised to be addressed in the problem solving therapy sessions.

Problem solving therapy is a 12-session group intervention designed to teach people strategies for solving interpersonal problems [9]. Participants are encouraged to learn the process of a) identifying negative feelings and using these as a cue for initiating the problem solving process; b) defining their problem clearly and accurately; c) setting specific goals for change; d) generating solution options; e) considering the consequences of each option; and f) selecting potentially effective options and organising these into a means-end action plan. Participants are then expected to implement the action plan and are offered individual support sessions to help with implementation. Progress with the action plan is reviewed in the next group session.

### Assessments

#### Screening

Screening for personality disorder is via the International Personality Disorder Examination (IPDE) [27]. This is a 99-item, semi-structured interview that allows both diagnostic and dimensional scores to be extracted for each personality disorder according to either DSM or ICD criteria.

#### Primary outcome

The primary outcome is social functioning, measured by the Social Functioning Questionnaire (SFQ) [23]. The SFQ is an 8-item self-report scale, with items covering the domains of home, work, leisure, and relationships. Respondents rate the extent to which they have experienced problems in each area over the last two weeks on a scale from 0 to 3. SFQ scores correlate well with measures of psychiatric distress and are stable over time. A reduction (i.e., an improvement) of 2 points or more on the SFQ at follow up 72 weeks post-randomisation is our specified clinically significant change.

#### Secondary outcomes

Measures of a number of secondary outcomes are listed below.

##### Receipt and cost of services

(Client Service Receipt Inventory; CSRI [31]). One measure used to capture service use is the CSRI, which records health and social care, criminal justice, informal care services, employment and benefits as reported by the participant. This information will be used in the cost-effectiveness analysis. Service use will be assessed for the period 6 months prior to baseline, and at three points after treatment (immediately after, at 4 months and at 72 weeks). The long-term follow up is necessary to pick up potential improvement overall, rather than capture a temporary increase at the end of treatment.

##### Scheduled and unscheduled service use (Record Check)

People with PD are often long-term users of services, but they can be chaotic users of those services. Hence, one valuable outcome would be a more systematic use of the services available. We hope to find a reduction of unscheduled service usage and an increase in scheduled service usage. Data on mental health service use, Emergency Department attendances and hospital admissions will be collected through a review of mental health service and GP records to ascertain use of scheduled and unscheduled services. Service use data will be collected retrospectively for the duration of involvement in the trial, from baseline to 72 week follow-up.

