### Study Hypotheses

Our primary hypothesis is that, compared with those in treatment-as-usual, those in PEPS therapy will show a greater improvement in social functioning post-therapy and at follow-up 72 weeks post-randomisation. Secondary hypotheses are that, compared with those in treatment-as-usual, those in PEPS therapy will show the following changes both immediately after therapy and at follow-up: (a) a greater reduction in receipt of unscheduled services; (b) a greater increase in receipt of scheduled services; (c) a greater improvement in quality of life; (d) a greater improvement in referrers' ratings of functioning; (e) a greater reduction in anxiety and depression; and (f) improvement on client-ratings of self-identified three key problems. Regarding intermediate changes, we hypothesise that, compared with those in treatment-as-usual, those in PEPS therapy will show: (a) better therapist alliance after psycho-education; and (b) a greater improvement in social problem solving at end of therapy. We also expect PEPS therapy to show an acceptable level of cost-effectiveness, based on thresholds that appear to guide National Institute for Clinical Excellence (NICE) recommendations.

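### The service-use record check starts at baseline and does not set PEPS contacts apart, which costs precision and may inflate the scheduled-use comparison

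*Protocol article*

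**What the plan says.** Study Hypotheses sets out two service-use hypotheses, both relative to treatment as usual (TAU): "a greater reduction in receipt of unscheduled services" and "a greater increase in receipt of scheduled services". The Record Check section repeats the direction: "We hope to find a reduction of unscheduled service usage and an increase in scheduled service usage". It gives the rationale as more orderly use of the services on offer.

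The same section names the source. Data on mental health service use, emergency attendances and admissions "will be collected through a review of mental health service and GP records to ascertain use of scheduled and unscheduled services". It also fixes the window: "Service use data will be collected retrospectively for the duration of involvement in the trial, from baseline to 72 week follow-up". It does not define a scheduled contact and does not mention PEPS sessions.

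Interventions describes four individual psycho-education sessions, and then: "Problem solving therapy is a 12-session group intervention". Individual support sessions are offered as well, with no number given. The comparison arm receives TAU only.

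Analyses compares mean totals of the secondary outcomes between arms at 72 weeks, adjusted for centre and sex. No term for prior use is named. The self-report service inventory (CSRI) does look back: "Service use will be assessed for the period 6 months prior to baseline". The economic paragraph costs PEPS sessions apart from the other services.

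**The concern.** Two features of the record check fit poorly with the hypotheses it serves.

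**Window.** The hypotheses speak of change, but the records are read only from baseline. No within-person change can be computed from this source, and no record-based prior count is available as a covariate. Past use is usually a strong predictor of later use, so leaving it out wastes information on outcomes that are likely to be skewed.

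**Content.** PEPS is itself a course of booked contacts given to one arm. The exclusion criteria remove people who are in, or likely to start, a specific psychological programme for personality disorder, so the TAU arm is unlikely to have a matching block of sessions. If PEPS contacts sit in the reviewed mental health records and are counted, hypothesis (b) could be supported with no change in how participants use any other service. That would not answer the question the section poses.

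Service use is the first secondary outcome listed in the abstract, so the reading of these results matters.

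**Working it through.** **1. The plan's own figure.** The only power calculation is for the SFQ: difference 2, SD 4.53, two-sided 1%, power 80%.
n per arm = 2 × (2.576 + 0.842)² × 4.53² / 2² ≈ 119.9, rounded up to 120. This reproduces the stated 120. Allowing for 30% dropout, 120 / 0.7 = 171.4, or 172 against the stated 170, which is close enough (170 × 0.7 = 119). No calculation is given for service use. I use 120 per arm below.

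**2. Is the between-arm comparison valid without a pre-period?** Under randomisation, expected prior use is equal in the two arms. Hence
E[post − pre | PEPS] − E[post − pre | TAU] = E[post | PEPS] − E[post | TAU].
The planned comparison of totals therefore estimates the relative reduction or increase without bias. A simulation agrees. It used 4,000 trials of 120 per arm, with Poisson counts and person-level rates drawn from a gamma distribution. Prior mean was 3, follow-up mean was 3 under TAU and 2 under PEPS, so the true difference was −1.0.

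| Comparison | Mean estimate | SE |
|---|---|---|
| Follow-up totals only | −0.99 | 0.396 |
| Change from pre-period | −1.01 | 0.319 |

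Both recover the true difference. The variance ratio is (0.319 / 0.396)² ≈ 0.65, so the pre-period removes about 35% of the variance under this model.

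**3. Precision under other correlations.** With prior use as a covariate in a linear model, residual variance is multiplied by 1 − r². The article gives no r, so these are assumptions:
- r = 0.4: 1 − 0.16 = 0.84, a 16% reduction.
- r = 0.6: 1 − 0.36 = 0.64, a 36% reduction.

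A raw change score multiplies variance by 2(1 − r) relative to follow-up alone: 1.4 at r = 0.3, 1.0 at r = 0.5, 0.6 at r = 0.7. It can therefore lose precision, and the prior count should enter as a covariate.

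**4. Possible contribution of PEPS contacts.** Core sessions: 4 + 12 = 16 for a full attender, 8 at half attendance, 4 at a quarter, before support sessions. If these are counted and nothing else differs between arms, the chance of a significant result is approximately Φ(d / (SD × √(2/120)) − 1.96) at two-sided 5%. Attendance, SD and the 5% level are assumptions.

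| Added contacts, d | SD 10 | SD 20 | SD 30 | SD 40 |
|---|---|---|---|---|
| 16 | 100% | 100% | 98.5% | 87% |
| 8 | 100% | 87% | 54% | 34% |
| 4 | 87% | 34% | 18% | 12% |

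Example: d = 8, SD = 20. The SE is 20 × 0.1291 = 2.582; 8 / 2.582 = 3.098; 3.098 − 1.96 = 1.138; Φ(1.138) ≈ 0.87. If PEPS contacts are excluded, d = 0 and the effect disappears.

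**The case against.** The strongest reply has four parts.

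- **Validity.** The hypotheses are comparisons with TAU in individually randomised participants, and Analyses plans a between-arm comparison. A missing pre-period does not bias it. This stands in full. A reader might infer from the baseline-only window that the reduction in unscheduled use cannot be measured. The documents do not support that: the relative reduction is estimable, and only within-person change in the records is not.
- **A prior measure exists.** The CSRI covers the 6 months before baseline. This stands in part. The CSRI is self-reported and is not stated to split scheduled from unscheduled use, and Analyses names no prior-use covariate for secondary outcomes from either source.
- **PEPS contacts may not be counted.** A reader might also infer that the increase in scheduled use is built in. The article does not say that PEPS sessions are entered in the reviewed records or that they count as scheduled use. Attendance is gathered separately as a process measure, and PEPS is costed separately. An extraction rule may sit in the full protocol, analysis plan or data form, none of which is shown. This stands, so the inflation is conditional.
- **The sizes are assumed.** Attendance, SD and correlation are not in the article, and PEPS might displace some usual contacts, which would shrink the net gain. This also stands. The chances in the table run from 12% to 100%.

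The explicit window remains, as does the adjustment for centre and sex only. So does the fact that a literal reading of the record check would admit PEPS contacts.

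**Conclusion.** The point holds as a matter of precision and interpretation for the record-based secondary outcomes.

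The window is stated outright. It leaves the record check unable to show whether anyone's use fell or rose, and the planned adjustment forgoes a gain of 16% to 36% in residual variance if the correlation between prior and later use is 0.4 to 0.6. Those percentages come from a linear model and are only a guide for skewed counts.

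The possible inflation of scheduled use is 0 if PEPS contacts are left out. It is up to 16 contacts per full attender, plus support sessions, if they are logged and counted. It does not plainly touch unscheduled use. The primary outcome (SFQ) and the sample size are unaffected.

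**What to change.** 1. Define scheduled use as excluding all PEPS psycho-education, group and support contacts, and report those separately, as the costing already does. If the full protocol or extraction form already says so, a sentence confirming it is enough.
2. Extend the record review to the 6 months before baseline, matching the CSRI window, and adjust follow-up use for that count as a covariate alongside centre and sex.
3. If the look-back is not feasible, adjust for the baseline CSRI service use already collected, and word the record outcome as a between-arm difference in use over 72 weeks.

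The cost is one definition, a little extra abstraction time in records that are being opened anyway, and a check that consent covers the earlier period. The fallback needs no new data.
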